#### Secondary outcome

functional status (spirometry), quality of life (St George respiratory questionnaire [27], and EuroQoL-5 D [28]) and the clinical progress with SeguiEPOC questionnaire.

#### Independent variables

age, sex, educational level, comorbidity, smoking history, COPD severity grade (according to SEPAR guidelines [29]), prescribed medication, family support (Family Apgar Test [30]): social support (DUKE-UNC Test [31]).

### Intervention

#### Activities

The intervention has two main activities: a group session followed by individual visits.

##### Group session

the session will last 2 hours including the patient's reception, the material distribution, the intervention and the farewell. The intervention is structured in three parts: the first part will be conducted following the focus group methodology. The number of patients will be about 6 to 9 per group. In the second part, patients will receive information about their disease and treatment with the aid of the distributed material. The third part will be conducted as a training session about inhalation technique.

##### Individual visits

will last 30 minutes approximately, it will depend on the topics related to adherence that we will need to work with every patient. These encounters will be videotaped to facilitate the collection of the data. In addition to written informed consent including in the recruitment visit, we will ask for their verbal informed consent all the times that we will videotape a visit.

#### Intervention Content

The content of the intervention can be divided in three elements that include the most relevant aspects related to the non-adherence in patients with COPD: motivational and cognitive aspects, and skill development.

##### Motivational Aspects

We mean to find out why the recommended therapeutic regime is not accomplished, in order to use the individual motivational aspects that could improve the adherence over the next follow up visits.

This aspect of the intervention will be developed along the first part of the group session and in the individual visits with different methodologies. In the first part of the group session, we will use qualitative methods by the *focus group technique *to explore the beliefs and attitudes of patients. In the individual visit, we will use this knowledge to design individual interviews to work on motivational aspects to try to improve treatment adherence. These individual interviews will be conducted in the follow-up visits (V1, V2 and V3).

Qualitative research methods have proved to be useful in the health care field. These methods provide in-depth knowledge about perceptions, beliefs and values of the persons or groups involved [32]. Taking into account the importance to explore behaviours and attitudes of our target population we consider the group interview (*focus group*) will be the most adequate technique to gather the information. These techniques explore dynamics interactions between group members, consider issues that may underlie individual preferences and explore areas of agreement and dissent [33], to reveal patient's experiences and points of view about their illness and treatment.

The research team has determined the basic topics to explore in the focus group. These are about adherence and the strategies to cope with the disease, and they are made as a semi-structured questionnaire (Figure 2). The content of this questionnaire might be adapted depending on the findings that could arise during the development of the focus group [33].

**Figure 2 F2:**
[figure not shown]
**Focus group interview script**.

An interviewer and a collaborator will be present in each group. They are both specially trained in qualitative techniques and in the use of inhaler devices. The training in motivational techniques has been done under one of the project researcher's supervision who is an expert in communication techniques at the Teaching Unit of Community and Family Medicine (Málaga).

The interviewer will introduce the study's objective, will explain the need to video-record the session and will give information about data confidentiality. The patients are asked for their consent to videotape the session. After the group sessions the two investigators will discuss their impressions and notes about each group.

The data will be extracted using a form designed by the research team using the group session questionnaire. All the participants' opinions will be collected. Each group will be reviewed and the data will be collected from the videotape by at least two members of the research team. After the data collection, these researchers will discuss their opinions of each patient and will agree a motivational strategy for the individual visits.

In the individual interviews, we will work with the patient on all aspects that we have detected in the focus group using the techniques of the motivational interview. These visits will be video-recorded and the data will be collected in the same way as in the focus group to design the strategy for the next follow-up visit.

##### Cognitive Aspects

Information is given about the disease so the patients can get to know it better and be more conscious about the importance of the scheduled treatment.

We have designed an audiovisual presentation to inform the patients about the most important issues of their illness and its treatment and a written dossier with the oral presentation content which will be given to the patient.

In the follow-up visit we will ask the patient if he has doubts about his illness or about the information he was given in the group session. Any questions they have are answered straightaway.

##### Skills Training

In the group session, the patients will receive inhalation technique training, about how they use their inhalers, why a good technique is important and will practice the proper technique according to SEPAR guidelines [34]. The training in the use of inhaler devices has been done at the Pediatrics Pneumology Service of Hospital Materno Infantil (Málaga).

We will perform training in three steps:

- Patients will be asked how they use their inhalers. Using a variety of placebo inhalers, all of them will demonstrate how they use them to the instructor.

- When all patients have done the demonstration, the trainer will ask about the problems and mistakes with each technique. At the beginning, these questions will be for individuals, but when all patients have answered individually, the questions will be made general and opinions can be expressed about any demonstration.

- The trainer will demonstrate the proper technique. Each device will be used and its technique will be explained step by step. The importance of following the correct technique every time the patient uses the inhaler device will be emphasized.

Finally the patients can ask questions and they will practice the techniques until they are correct or until the patient becomes tired.

In the follow-up visits we will review the inhalation technique and we will solve any mistake or doubt as explained previously. The objective here is for the patients to identify their mistakes, and if they cannot, to remind them the proper technique by as many demonstrations as are necessary.

### Recruitment

Patients will be contacted using their health center records. They will be invited to participate in the study after a brief explanation by telephone about the research aims and they will receive an appointment in the health center. At this first appointment (inclusion visit) patients will receive more detailed information about the study and if they agree to participate, they will sign the written consent.

At this point, subjects will be divided randomly into two groups using the block randomization technique. The blocks consist of 4 patients, two subjects per group [Intervention (I) and control (C)]: (IICC); (CCII); (CICI); (ICIC); (ICCI); (CIIC). Consequently, the numbers in the two groups never differ at any time by more than two. The blocks will be marked with a number from 1 to 6 and we will choose blocks at random to create the allocation sequence using a sequence of random numbers generated by Microsoft Excel 2003 program with the function fx:RAND(). We will need 35 random blocks; and the final list of the included patients in each arm of the trial will be set in advance. The researcher who will allocate the patient will have the open-list of randomization, but there will be no change of patient group related with the subjects characteristics. Because the patients are from 6 health centers, the randomization and the presence of the intervention and control subjects in all the health centers will be guaranteed.

After randomization all the study data will be recorded and the adherence will be measured in both groups.

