### Participants

140 patients with COPD selected by a non-probabilistic consecutive sampling method. The inclusion criteria were searched in the patient's clinical record as: having been diagnosed of COPD by spirometry following the SEPAR (Sociedad Española de Neumología y Cirugia Torácica) guidelines [23], receiving clinical assistance in primary care centers in Malaga area, having been prescribed inhaled and scheduled treatment; and having agreed to be part of the study by giving signed written consent. Exclusion criteria: other respiratory conditions which are not included in the COPD definition (bronchiectasis, asthma or cystic fibrosis) and cognitive impairment problems registered in their clinical record (Dementia, Alzheimer, Parkinson, Cognitive decline).

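### The researcher who allocates patients holds the open randomization list, so allocation is not concealed and selection into the arms is not prevented

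*Protocol article*

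**What the plan says.** All of this is in the protocol article.

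- **Recruitment, the sequence.** "The blocks consist of 4 patients, two subjects per group". The six possible blocks are listed and drawn with spreadsheet random numbers. "We will need 35 random blocks; and the final list of the included patients in each arm of the trial will be set in advance".
- **Recruitment, the list holder.** "The researcher who will allocate the patient will have the open-list of randomization", followed by the only stated protection: "but there will be no change of patient group related with the subjects characteristics".
- **Recruitment, the order of events.** Patients are identified from health centre records, invited by telephone and given an appointment. At that visit, "if they agree to participate, they will sign the written consent". Randomization follows at that point. Study data, including adherence, are recorded in both groups after it.
- **Participants.** "140 patients with COPD selected by a non-probabilistic consecutive sampling method".
- **Study limitations.** Selection bias is discussed only as a consequence of missing data. Allocation is not mentioned.

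No envelopes, central or telephone release, or independent list holder is described.

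**The concern.** Randomization protects the comparison only if the next assignment is unknown when a patient is invited, judged eligible and asked for consent. Here the sequence is open to the person who allocates. The promise not to move patients between groups addresses tampering after assignment. It leaves untouched the choices made before assignment: whom to call next, when to book, how to present the study, and whether to enrol a doubtful case.

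This matters more than usual because the article itself treats motivation as a main driver of adherence, and adherence is the primary outcome. If willing or easily reached patients were enrolled more often into one arm, the primary chi-square comparison would mix that difference with the effect of the intervention. Recording baseline after randomization adds a second weakness: baseline values, which would be used to look for imbalance, are themselves collected when the arm is known.

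**Working it through.** **1. The plan's own figure.** 35 blocks × 4 patients = 140, which matches the stated sample size exactly. One set of 35 blocks therefore covers the whole trial.

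**2. What the list holder knows.** The list is complete before enrolment and open to the allocator. The share of upcoming assignments known in advance is 140/140 = 100%. Block size is irrelevant at this stage.

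**3. What remains if only the list is hidden.** Group sessions make the arm visible, so staff can track past assignments. For the six blocks of 4, count the positions fully determined by the earlier ones:

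| Block | Determined positions |
|---|---|
| IICC | 2 (third and fourth) |
| CCII | 2 (third and fourth) |
| CICI, ICIC, ICCI, CIIC | 1 each (fourth) |

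Total: 2 + 2 + 4 × 1 = 8 of 6 × 4 = 24 positions, or 33.3%.

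The best guess is right with probability 1/2, 2/3, 2/3 and 1 at positions one to four. The mean is (0.500 + 0.667 + 0.667 + 1.000)/4 = 70.8%, against 50% with no information.

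**4. What selection could do to the primary test (illustration).**

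- From the article: 140 patients, 15% losses, 5% significance level, chi-square test. 140 × 0.85 = 119, or about 60 per arm.
- Assumed: adherence near 50%, no treatment effect, and a difference s in underlying adherence between arms created by selective enrolment.

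With n = 60, p₁ = 0.5 − s/2 and p₂ = 0.5 + s/2:

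- SE₀ = √(2 × 0.25/n) = 0.0913, so the critical difference is 1.96 × 0.0913 = 0.179
- SE₁ = √([p₁(1 − p₁) + p₂(1 − p₂)]/n)
- P(significant) = Φ((s − 0.179)/SE₁) + Φ((−s − 0.179)/SE₁)

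For s = 0.10, SE₁ = 0.0908. The two terms are Φ(−0.87) + Φ(−3.07) = 0.192 + 0.001 = 0.19.

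| Assumed shift s | False-positive rate |
|---|---|
| 0 | 5% |
| 5 points | 8% |
| 10 points | 19% |
| 15 points | 37% |

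The article gives no basis for choosing a value of s. The table shows only how sensitive the test is.

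**The case against.** The strongest reply is that the steering mechanism is inferred. The article names the researcher who allocates. It does not say that this person also telephones, books or judges eligibility. Sampling is stated to be consecutive, eligibility is read from clinical records, and consent precedes allocation. These points narrow the room for choice, and they stand. They do not replace concealment: consecutive sampling does not fix the order of calls and appointments, and nothing keeps the list from those who recruit.

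A second reply is that the article condenses a fuller protocol. That would excuse silence about concealment, but the article states affirmatively that the list is open.

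A third is that adherence is measured at inclusion in both groups and a logistic model is planned, so imbalance could be seen and adjusted for. This is partly right. It would be too strong to say that analysis is helpless. But the listed independent variables include neither baseline adherence nor motivation, and the model can adjust only for what is measured.

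Two stronger readings are tempting and not supported:

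- **That the bias will favour the intervention.** Nothing in the article fixes its direction, or shows that any steering takes place.
- **That the statement on centres is false and centre imbalance confounds the result.** The text says "the presence of the intervention and control subjects in all the health centers will be guaranteed". That claims presence of both arms, not balance. At about 140/6 ≈ 23 patients per centre, presence is all but certain. How uneven a centre could be depends on recruitment order, which is not stated, and chance imbalance under randomization adds variance rather than systematic bias.

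**Conclusion.** The concern holds for the open list. As described, allocation is unconcealed: the list holder knows every upcoming assignment, and the stated safeguard does not act before enrolment. This should be corrected before patients are allocated, because concealment cannot be restored afterwards and the causal reading of the primary comparison depends on it.

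The certain part is the 100% foreknowledge of the list holder. The 33.3% for fixed blocks of 4 becomes relevant only once the list is hidden, and assumes that someone knows the block size and follows past assignments. The false-positive rates of 8% to 37% rest on assumed shifts of 5 to 15 points, and are not estimates of bias in this trial.

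**What to change.** - Replace the open list with concealed allocation. The list is kept by someone who does not recruit, or each assignment is released by telephone or in sequentially numbered, opaque, sealed envelopes.
- Reveal the arm only after consent and after baseline recording. Consent already comes first. Baseline recording would have to move ahead of randomization.
- Replace the sentence that relies on not changing a patient's group with a description of the concealment procedure.
- Vary the block size at random, for example 4 and 6, and do not disclose the sizes to recruiting staff.
- Optional refinement: a separate list for each health centre.

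**Cost.** Slight administrative work, with no extra patients and no change to N = 140. Arm sizes may no longer be exactly 70:70. With one list of mixed blocks of 4 and 6 stopped at 140, only the last block can be incomplete. It then holds an even number of patients, so the arms differ by at most 2. Separate centre lists could leave several incomplete blocks and a somewhat larger difference.

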### Sample size

it was calculated to detect an adherence percentage difference between the two groups of 25%, with a statistical power of 80% and a confidence level of 95%, assuming a percentage of expected losses of 15%. The final sample size was 140 patients with COPD that meet the selection criteria mentioned above.

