#### Intervention Group

After the inclusion, the first part of the intervention (group session) will be carried out in each health center and the intervention group will receive appointments for:

Visit 1: It will take place 3 months after the intervention. It will involve the measure of adherence and other variable changes, encouragement about inhalation techniques and motivational aspects related to treatment adherence.

Visit 2: It will take place 6 months after the intervention. It will involve the measure of adherence, other variable changes and encouragement about inhalation techniques and motivational aspects related to treatment adherence.

Visit 3: It will take place after 1 year follow-up. All the study data will be recorded and encouragement about inhalation techniques and motivational aspects related to treatment adherence.

There was a pre-adherence visit prior to all visits as explained previously.

Adherence will be measured at each visit to control its evolution during the follow-up period. All individual follow-up visits will be videotaped to identify the motivational aspects and skills which each patient needs to be applied at the next visit.

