### Statistical Analysis

A descriptive statistical analysis will be performed for all the study variables. We will calculate the mean, median and standard deviations for quantitative variables, and the absolute and relative frequency for qualitative variables.

The 95% confidence level will be applied. The analysis will be made under an intention-to-treat procedure. The between-group comparison for the primary outcome will be explored using the Chi Square Test. The Relative Risk Reduction (RRR), the Absolute Risk Reduction (ARR) and the Number Needed to treat (NNT) will be calculated. Inferences for the secondary outcomes will be made using an analysis of variance (ANOVA). Finally a logistic regression model will be performed for the primary outcome [treatment adherence (yes/not)], considering the intervention as the predictive variable and the rest of the independent measures as the possible modifying factors. We will use the usual 5% significance level (α = 0.05) and the SPSS statistical package, version 15.0, to run the proposed analysis.

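### One list of 35 blocks of four balances the arms overall but does not guarantee both arms in each of the six health centres, as the protocol says it does

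*Protocol article*

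**What the plan says.** Under Recruitment, patients are allocated in blocks of four, two per arm, drawn at random from the six possible patterns. "We will need 35 random blocks", the section says; the list is fixed in advance and held openly by the researcher who allocates. The section notes that the two arms can never be more than two patients apart. It then gives the six-centre origin of the patients as the reason why "the randomization and the presence of the intervention and control subjects in all the health centers will be guaranteed". It mentions no list, block or stratum by centre.

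Three other places bear on this:

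- Sample size: "The final sample size was 140 patients with COPD".
- Intervention Group and Group session: "the first part of the intervention (group session) will be carried out in each health center", and "The number of patients will be about 6 to 9 per group".
- Statistical Analysis: "The between-group comparison for the primary outcome will be explored using the Chi Square Test". Centre is not among the listed independent variables.

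**The concern.** The protocol claims a property of its randomisation and describes a mechanism that does not deliver it. This is a wrong statement, not a detail left to a fuller document. Drawing patients from six centres is no reason why each centre should receive both arms. A trial-wide list balances the trial; when centres share it as patients arrive, the split within any one centre is left largely to chance.

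At stake are the accuracy of the stated design and the balance of the arms within centres, which may differ in prescribing, devices and patient mix. In a very small centre, the existence of any within-centre comparison is also at stake.

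**Working it through.** **Inputs from the protocol.** 140 patients, six centres, blocks of four at 1:1, 35 blocks. **Not given, so assumed:** centre sizes, and the order in which centres recruit.

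**The plan's own figures.** 140 / 4 = 35 blocks exactly, and one list of blocks of four keeps the overall difference to at most 2. Both statements fit a single trial-wide list. Separate lists for centres of 24, 24, 23, 23, 23 and 23 would need 6 × 6 = 36 blocks and would not keep the overall difference to 2. The 140 itself is not in dispute. With two-sided 5%, 80% power and a 25-point difference, rates of 25% and 50% give 58 per arm and 116 / 0.85 = 137; rates of 30% and 55% give 61 per arm and 122 / 0.85 = 144.

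**Parallel recruitment, equal centres.** With random arrival order, the intervention count in a centre of 23 is close to hypergeometric:

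- variance = 23 × 0.25 × (140 − 23) / 139 = 4.84, SD 2.2
- 95% range = 11.5 ± 1.96 × 2.2, about 7 to 16

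In 20,000 simulated lists, the mean within-centre difference was 3.5. Some centre differed by 6 or more in 70% of trials and by 8 or more in 38%. An absent arm never occurred.

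**Parallel recruitment, chance of an absent arm.** For a centre of m patients the chance is approximately 2 × C(70, m) / C(140, m):

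| m | chance |
|---|---|
| 3 | 24.5% |
| 4 | 12.0% |
| 5 | 5.8% |
| 6 | 2.8% |
| 7 | 1.3% |
| 10 | 0.14% |
| 12 | 0.03% |
| 23 | about 3 × 10⁻⁸ |

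Chance that at least one centre lacks an arm, by simulation:

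| Assumed centre sizes | Trials with an absent arm |
|---|---|
| 50, 40, 25, 13, 7, 5 | 7% (formula: 5.8 + 1.3 = 7.1%) |
| 55, 40, 25, 10, 6, 4 | 15% (formula: 12.0 + 2.8 + 0.1 = 14.9%) |
| 70, 40, 15, 8, 4, 3 | 34% |
| 40, 30, 24, 18, 16, 12 | 0.04% |
| 50, 36, 18, 12, 12, 12 | 0.09% |

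The most extreme set with every centre at 12 or more is 80 and five of 12, for which the formula gives about 5 × 0.03% = 0.15%.

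**Centres filled one after another.** A run of consecutive slots is made of whole blocks, which are balanced, plus at most one part-block at each end. Each part-block adds at most 2, so the difference is at most 2 + 2 = 4. Any centre with 5 or more patients then has both arms.

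**Blocks of four within each centre.** The difference in a centre is at most 2, and any centre with 3 or more patients has both arms. The overall difference could reach 6 × 2 = 12 in theory; it averaged 1.1 to 1.9 in simulation.

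**Effect on the primary test.** Simulated with equal centres, centre adherence assumed to run from 20% to 60%, and a 25-point effect for power:

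| Scheme and test | Type I error | Power |
|---|---|---|
| Single list, chi-square | 4.9% | 85.1% |
| Single list, Mantel-Haenszel | 5.2% | 86.1% |
| Centre blocks, Mantel-Haenszel | 5.1% | 87.0% |

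The gain is 87.0 − 85.1 = 1.9 points. With no spread between centres there is none: 85.3% for the first scheme, 85.1% for the last.

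**The case against.** The strongest reply is that the claim is true in practice. A session of 6 to 9 intervention patients in each centre suggests at least 2 × 6 = 12 patients per centre, and at that size an absent arm is very rare. This stands, and it confines the absent-arm risk to centres smaller than the plan seems to foresee. It does not make the guarantee strictly true, and it does not address uneven splits.

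The 70% figure depends on fully interleaved recruitment. That also stands: the protocol states no order, and filling centres in turn removes most of the imbalance. The single list is itself an inference, though a strong one from 35 × 4 = 140, one list set in advance, and the overall limit of two.

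A reader might go further in three ways that the documents do not support:

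- **That the primary comparison is biased or invalid.** Chance imbalance between centres under valid randomisation does not bias the test, and the type I error stays near 5%.
- **That sessions could not be filled.** The session size is approximate and nothing limits a centre to one session. With equal centres, 7 to 16 intervention patients mostly make one or two workable groups, and no clear gain from centre blocks was shown.
- **That leaving centre out of the chi-square test is an error in itself.** An unstratified test after unstratified randomisation is legitimate, and adjustment for centre may be set out in an analysis plan that is not shown.

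The open list is a separate weakness. Concealing it would not make the guarantee true, and blocking by centre would not conceal it.

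**Conclusion.** The point holds in a limited form. The protocol states a guarantee that its allocation scheme, as described, does not provide. Arms can be clearly uneven within centres under parallel recruitment (about 70% of trials with some centre 6 or more apart, for equal centres and random order), but need not be (4 at most if centres are filled in turn). Loss of an entire arm matters only for centres of about 3 to 7 patients. Validity is intact and the loss of precision is small. The finding rests on reading the 35 blocks as one trial-wide list and on assumed centre sizes and arrival order. It is a modest defect that is worth correcting because the correction is cheap.

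**What to change.** Generate a separate blocked sequence for each of the six centres, preferably with varying block sizes, and keep it from the person who enrols. Account for centre in the primary comparison, by a Mantel-Haenszel test or by centre in the logistic model.

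Two sentences under Recruitment must then change. The number of blocks becomes the sum over centres (36 for near-equal centres; 35 to 39 across the sizes examined). The limit of two applies within a centre if blocks are of four. With varying sizes the limit is half the largest block, and the overall difference can be larger.

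If the single list is kept, withdraw the word guaranteed and say that balance is ensured only for the trial as a whole.

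The cost is six lists in place of one, some rewording and slightly looser overall balance. Allocation within a centre becomes more predictable if blocks stay fixed at four, which is the reason for varying them.
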